## Abstract

**Background::**

Cancer-related fatigue (CRF) is essentially universal in cervical carcinoma patients. It develops rapidly, with physical and mental manifestations including generalized weakness, diminished concentration or attention, and it has a negative impact in overall quality of life. Buzhong Yiqi Decoction (BYD), a classical Chinese medical prescription, could be used for allergic rhinitis, gut microbiota disorders, and chronic obstructive pulmonary disease. We preliminarily found that BYD could relieve CRF in cervical carcinoma patients. However, there are few trials on whether BYD could relieve CRF and improve immunity in cervical carcinoma patients.

**Methods::**

This is a double-blinded, randomized, controlled clinical trial. From December 1, 2021 to May 31, 2022, cervical carcinoma patients with CRF will be assessed for randomization into treatment group (BYD) and control group (BYD simulation) in a 1:1 ratio. The outcomes are cancer fatigue scale, self-rating anxiety scales, self-rating depression scales, Pittsburgh sleep quality index, and immunity index (CD3^+^, CD4^+^, and CD8^+^) before and after the treatment. Statistical analysis will be performed using SPSS v22.0 software.

**Results and conclusions::**

The study will clarify the efficacy and safety of BYD in improving CRF and immunity in cervical carcinoma patients.

**Trial registration::**

OSF Registration number: DOI 10.17605/OSF.IO/QFNMD.

## Introduction

1

Cervical carcinoma, a malignant tumor that develops in the cervix, is mainly related to long-term infection. It is a common malignant tumor all over the world, with a high incidence, which has seriously affected women's physical and mental health.^[1,2]^ In recent years, chemotherapy has gradually become one of prior treatment methods for cervical carcinoma.^[3–5]^ It has been reported that low-dose chemotherapeutics could increase the sensitivity of radiotherapy in cervical carcinoma patients. With the continuous development of concurrent radiotherapy and chemotherapy, the efficacy and local control rate of radiotherapy have gradually increased, and the recurrence rate has initially decreased. Also, a large number of clinical studies have shown that concurrent radiotherapy and chemotherapy can significantly improve the survival rate of patients with advanced cervical carcinoma.^[6,7]^

Fatigue is one of the most common side effects of malignant tumor and its treatment, known as cancer related fatigue (CRF). It's a subjective experience self-reported symptoms.^[8,9]^ In recent years, CRF has gradually received clinical attention and intervention. CRF is widespread in cancer patients, and it is even a more common side effect in patients receiving chemotherapy and radiotherapy. It's estimated that the prevalence ranges from 25% to 99% in cancer patients after treatment.^[10,11]^ In cervical carcinoma patients, CRF was reported by 23% of long-term survivors at a mean of 11 years after treatment, and 28% in patients with chemoradiation.^[12]^ CRF develops rapidly, with physical and mental manifestations including generalized weakness, diminished concentration or attention, and it has a negative impact in overall quality of life.

A variety of interventions have been used for CRF, including physical activity, psychosocial and pharmacological interventions, yet with limited or unclear feasibility and efficacy.^[12]^ Traditional Chinese medicine (TCM) could control the development of cervical carcinoma. As an adjuvant treatment, it could also reduce adverse reactions and side effects of radiotherapy and chemotherapy, improve the long-term curative effect and the quality of life. Buzhong Yiqi Decoction (BYD), a traditional Chinese prescription, is composed of Huangqi (*Astragalus membranaceus*), Baizhu (*Atractylodes atractylodes*), Chenpi (*Pericarpium citri reticulatae*), Shengma (*Rhizoma cimicifugae*), Chaihu (*Radix bupleuri*), Rensheng (*Ginseng*), Gancao (*Liquorice*), and Danggui (*Radix Angelicae Sinensis*). Clinically, BYD could be used for allergic rhinitis, gut microbiota disorders, and chronic obstructive pulmonary disease.^[13–15]^ We preliminarily found that BYD could be used for CRF in cervical carcinoma patients. However, few trials have been reported on whether BYD could reduce CRF in cervical carcinoma patients. In this study, we try to conduct a randomized controlled trial to clarify the efficacy and safety of BYD in relieving CRF and improving immunity in cervical carcinoma patients.

## Methods

2

### Trial design

2.1

This is a randomized, controlled clinical trial, and it has been approved by the Ethics Committee of the Hospital Affiliated to Jianghan University. The study will be carried out in accordance with the Declaration of Helsinki. It conforms to the SPIRIT 2013 Statement, and the results will be reported according to the CONSORT Statement extension for trials (Fig. 1). This study protocol has been registered with Open science framework Registry platform (OSF Registration number: DOI 10.17605/OSF.IO/QFNMD).

**Figure 1 F1:**
[figure not shown]
Flow diagram.

### Participants

2.2

#### Recruitment

2.2.1

From December 1, 2021 to May 31, 2022, cervical carcinoma patients diagnosed with CRF will be assessed for eligibility. Before randomization, all patients will sign a written informed consent, and they can freely choose whether to discontinue the trial at any time.

#### Inclusion and exclusion criteria

2.2.2

Patients will be included if they meet the following criteria:

1)primary diagnosis of cervical carcinoma in stage Ib–IVa;2)complained of fatigue and a diagnosis with CRF;3)aging from 18 to 70;4)with signed informed consent.

Patients will be excluded if they are:

1)complicated with other malignant tumors;2)received surgery before;3)with severe abnormal liver or kidney function;4)history of allergy to BYD.

### Randomization

2.3

For allocation, patients will be simply assigned into treatment group (BYD) and control group (BYD simulation) in a 1:1 ratio. The randomization sequence will be generated by a statistician uninvolved in the statistical analysis. The random numbers will be placed in opaque, sealed envelopes and kept in a safe place. Each participant had a 50% probability of receiving each intervention upon selection.

### Blinding

2.4

This is a double blinded, and dummied study. The physician, patients, and assessors will all be blinded to the allocation. To maintain blindness, the decoction and simulations will be provided as granules. The BYD-simulations are in the same appearance, package, color, taste, and administration with BYD.

### Interventions

2.5

Patients diagnosed with CRF in the treatment group will be treated with traditional Chinese prescription of BYD as granules, including Huangqi (*A membranaceus*) 15 g, Baizhu (*A atractylodes*) 10 g, Chenpi (*P citri reticulatae*) 10 g, Shengma (*R cimicifugae*) 6 g, Chaihu (*R bupleuri*) 12 g, Dangshen (*Radix codcnopsitis pilosulas*) 15 g, Gancao (*Liquorice*) 15 g, and Danggui (*R Angelicae Sinensis*) 6 g. The granules will be provided by the Beijing Tcmages Pharmaceutical Co., Ltd., and they will be orally taken by dissolving in 50 mL warm water, twice a day, for 14 days. While in the control group, BYD simulations made of amylum will be applied for patients with the same administration method.

### Outcome variables

2.6

The primary outcome is the change of fatigue scores measured by cancer fatigue scale before and after the treatment. The secondary outcomes are self-rating anxiety scales,^[16]^ self-rating depression scales,^[17]^ Pittsburgh sleep quality index,^[18]^ and immunity index (CD3^+^, CD4^+^, and CD8^+^) before and after the treatment. Blood routine, liver and kidney function, coagulation, and adverse events will also be recorded.

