### Sample size

2.7

In our preliminary study, the change of cancer fatigue scale scores in the treatment group was 6.65 ± 2.12, while 3.5 ± 1.53 in the control group. Considering a 2-sided *t* test, with 5% type I error at 80% power, and a potential dropout of 10%, the required total sample size will be 110.

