### Statistical analysis

2.8

Statistical analysis will be performed using SPSS v22.0 software. The measurement data is expressed as mean ± standard deviation, and Student *t* test, Wilcoxon rank-sum test, or Manne–Whitney *U* test after normality and homogeneity test. The count data is expressed as percentage (%) and *χ*^2^ test will be applied. *P* < .05 is considered statistically significant.

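### Change in fatigue score is compared without adjustment for the baseline score that is already collected: a valid analysis, but one that gives up precision and mis-corrects chance baseline imbalance

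*Protocol article*

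**What the plan says.** Section 2.6 (Outcome variables) defines the primary endpoint: "The primary outcome is the change of fatigue scores measured by cancer fatigue scale before and after the treatment". The anxiety, depression and sleep scales and the CD3+, CD4+ and CD8+ markers are also measured before and after treatment, so a baseline value is planned for each.

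Section 2.7 (Sample size) works on the same quantity. In the preliminary study "the change of cancer fatigue scale scores in the treatment group was 6.65 ± 2.12, while 3.5 ± 1.53 in the control group", and the calculation is described as "Considering a 2-sided *t* test, with 5% type I error at 80% power".

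Section 2.8 (Statistical analysis) covers all continuous data in one sentence, which begins "The measurement data is expressed as mean ± standard deviation, and Student" and goes on to "Wilcoxon rank-sum test, or Manne–Whitney *U* test after normality and homogeneity test". No regression model, covariate or baseline adjustment appears anywhere in the article.

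Section 2.3 (Randomization) says "patients will be simply assigned into treatment group (BYD) and control group (BYD simulation) in a 1:1 ratio". No stratification by baseline fatigue is stated.

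**The concern.** Endpoint, sizing and tests all point to one analysis: an unadjusted comparison of change scores. That comparison amounts to subtracting the baseline score with a coefficient of exactly 1. In noisy symptom scales the regression of follow-up on baseline often has a slope below 1, and patients who start high then tend to improve more whatever they receive. Regression to the mean is plausible here because section 2.2.2 admits patients on account of their fatigue. The 3.5-point change in the pilot control group is compatible with it but does not prove it.

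Two things follow when the slope is not 1. The treatment contrast has a larger variance than it needs to have. And if one arm happens to start more fatigued, the estimate shifts: with a slope below 1, the more fatigued arm is favoured. Simple allocation leaves the baseline balance to chance.

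**Working it through.** **Inputs.** From section 2.7: mean changes 6.65 and 3.5, SDs 2.12 and 1.53, two-sided 5% level, 80% power, 10% dropout, total 110. Assumed, because the article does not give them: equal baseline and follow-up SDs (σ), and a baseline–follow-up correlation r of 0.3, 0.5 or 0.7.

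**Pilot quantities.** Difference = 6.65 − 3.5 = 3.15. Pooled SD = √((2.12² + 1.53²)/2) = 1.849. Standardised difference = 3.15/1.849 = 1.70.

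**The plan's own figure.** These inputs do not return 110. They need 6 per arm by the normal approximation, or 7 by the exact t calculation, which is 14 to 16 in total after 10% dropout. That is a separate matter. It bears on this point only because the pilot figures do not explain the chosen size. The total of 110 is taken as given below: 110 × 0.9 = 99 evaluable, about 49 per arm.

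**Precision.** Var(change) = 2σ²(1 − r). Residual variance after ANCOVA = σ²(1 − r²). The ratio is (1 + r)/2. The detectable difference for the change score is 1.849 × √(2/49) × 2.8016 = 1.05 points, and ANCOVA multiplies it by √((1 + r)/2).

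| r (assumed) | Variance ratio | Fall in standard error | Patients matching 110 by change score | Detectable difference, 49 per arm |
|---|---|---|---|---|
| change score | 1 | – | 110 | 1.05 |
| 0.3 | 0.65 | 19% | 72 | 0.84 |
| 0.5 | 0.75 | 13% | 83 | 0.91 |
| 0.7 | 0.85 | 8% | 94 | 0.97 |

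**Chance imbalance.** The standard error of the baseline difference between arms is √(2/49) = 0.20 baseline SD (0.19 with all 55 per arm). Given an imbalance Δ and a true slope β, the change-score contrast is shifted by (1 − β)Δ in size. With equal SDs β = r, and σ = 1.849/√(2(1 − r)), which is 1.56, 1.85 or 2.39. An imbalance of two standard errors therefore shifts the contrast by (1 − r) × 2 × 0.202 × σ = 0.44, 0.37 or 0.29 points, or 14%, 12% or 9% of 3.15.

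**Effect on power at the pilot difference.** 3.15/(1.849 × √(2/49)) = 8.4 standard errors. Power exceeds 99.9% with or without adjustment.

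**The case against.** The strongest reply is that nothing here is invalid. In a 1:1 randomised trial, comparing change scores is unbiased over randomisations and controls the type I error. Sections 2.6 to 2.8 agree with one another. Regression to the mean acts in both arms and does not bias the contrast on average. All of that stands.

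A second reply is that this is a condensed article, its analysis plan is not shown, and a t test used for sizing does not forbid an adjusted analysis. This carries some weight. But section 2.8 is not silent: it names the tests for continuous data, and all of them are unadjusted.

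Third, the loss is not universal. The two analyses have equal variance whenever the slope r × SD(post)/SD(pre) equals 1. With SDs of 1 and 1.25 and r = 0.8, Var(change) = 1 + 1.5625 − 2 = 0.5625 and Var(ANCOVA) = 1.5625 × 0.36 = 0.5625. A reader might infer that the change score always loses unless r is 1. That holds only with equal variances.

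Fourth, on the article's own pilot figures the choice would not alter the conclusion. That is correct, and it limits the importance of the point.

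**Conclusion.** The point holds as an efficiency improvement. The plan fixes an unadjusted change-score comparison although a better use of the same data is available. The size rests on an assumed r and on equal variances: 15% to 35% lower variance, and a detectable difference of 0.84 to 0.97 instead of 1.05 points, for r between 0.7 and 0.3. The benefit is real mainly if the true effect is nearer 1 point than 3.15, if the SD exceeds the pilot value, or for the secondary outcomes, which have no power statement.

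Two stronger readings are not supported. One is that the planned test is biased or invalid; it is valid on average, and the shift arises only conditionally on an observed imbalance. The other is that baseline imbalance is left uncorrected; a change score does correct for it, but by the wrong amount when the slope is not 1. At r = 0.5 with equal SDs, the resulting error is as large as with no correction and runs in the opposite direction.

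**What to change.** In section 2.8, make the primary analysis a linear model of the post-treatment (or change) cancer fatigue scale score on treatment arm and baseline score, and report the adjusted mean difference with its 95% confidence interval. Use the same model for anxiety, depression, sleep and the CD3+, CD4+ and CD8+ outcomes, each with its own baseline value. Keep the unadjusted change as a descriptive summary. The endpoint sentence in section 2.6 can stand, because for a given baseline covariate the treatment estimate is the same whether the post-treatment score or the change is modelled.

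The cost is one or two sentences. No extra data are needed, and the software already named can fit the model. Fixing it before unblinding also removes any later choice between adjusted and unadjusted results.

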### Sample size

2.7

In our preliminary study, the change of cancer fatigue scale scores in the treatment group was 6.65 ± 2.12, while 3.5 ± 1.53 in the control group. Considering a 2-sided *t* test, with 5% type I error at 80% power, and a potential dropout of 10%, the required total sample size will be 110.

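### The stated pilot figures need about 16 patients for 80% power, not 110, so the sample size and its power statement do not agree

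*Protocol article*

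**What the plan says.** Section 2.6 (Outcome variables) fixes the endpoint: "The primary outcome is the change of fatigue scores measured by cancer fatigue scale before and after the treatment". Section 2.7 (Sample size) bases the trial size on pilot values for that same variable: "the change of cancer fatigue scale scores in the treatment group was 6.65 ± 2.12, while 3.5 ± 1.53 in the control group". The design settings follow in the same section: a two-sided t test "with 5% type I error at 80% power". The section ends: "and a potential dropout of 10%, the required total sample size will be 110".

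Section 2.3 (Randomization) sets 1:1 allocation. Section 2.8 (Statistical analysis) gives the only definition of the ± notation in the document: "The measurement data is expressed as mean ± standard deviation".

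The article mentions no other target difference, no discounting of the pilot effect, and no safety, secondary-outcome or feasibility reason for enrolling 110.

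**The concern.** Everything needed for a two-sample calculation is printed, and 110 is presented as what those inputs require. Yet the pilot difference is large relative to its spread (3.15 points against SDs of about 2 and 1.5), and an effect of that size needs very few patients. A total of 110 looks out of line at first sight.

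This paragraph is the only quantitative justification for the primary comparison. If it is wrong, a reader cannot tell what effect the trial is designed to detect. An ethics committee cannot tell whether the patients beyond the calculated need are intended. Nor can anyone tell whether 110 rests on a different, unstated assumption under which the true power could be quite different from 80%.

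**Working it through.** **Inputs**

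| Input | Value | Section |
|---|---|---|
| Change, treatment arm | 6.65, SD 2.12 | 2.7 |
| Change, control arm | 3.5, SD 1.53 | 2.7 |
| Meaning of ± | SD | 2.8 |
| Test | two-sided t, alpha 0.05 | 2.7 |
| Power | 0.80 | 2.7 |
| Dropout | 10% | 2.7 |
| Allocation | 1:1 | 2.3 |

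**Attempt to reproduce 110**

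- Difference: 6.65 − 3.5 = 3.15.
- Pooled SD: √[(2.12² + 1.53²)/2] = √[(4.494 + 2.341)/2] = 1.849.
- Standardised effect: 3.15 / 1.849 = 1.70.
- Normal approximation, n per arm = (1.960 + 0.842)² × (2.12² + 1.53²) / 3.15² = 5.4, so 6 per arm. That is 12 evaluable, and 12/0.9 = 13.3, so 14 in total.
- Noncentral t, equal variances: 6 per arm gives 75.8% power and 7 per arm gives 83.3% (82.6% with the Welch form). So 7 per arm, 14 evaluable. Per arm 7/0.9 = 7.8, rounded up to 8, hence 16 in total.

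The stated total is 110/16 ≈ 6.9 times this figure.

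**Other readings at the stated alpha, sidedness and power (t-based, with 10% dropout)**

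| SD used | n per arm | Total |
|---|---|---|
| 1.53 (smaller arm SD) | 5 | 12 |
| 1.85 (pooled) | 7 | 16 |
| 2.12 (larger arm SD) | 9 | 20 |
| 2.61 (root of summed variances) | 12 | 28 |
| 3.65 (SDs added; not a valid SD) | 23 | 52 |

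None comes near 110. Totals of 112 to 114 appear only when the invalid SD of 3.65 is combined with 99% power at two-sided 5%, or with 95% power at two-sided 1%. Both contradict the stated settings.

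**What 110 delivers**

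- Evaluable patients: 110 × 0.9 = 99, about 49 to 50 per arm.
- Power for 3.15 points at SD 1.849, with 49 per arm: the noncentrality is 1.704 × √(49/2) = 8.43, far above the critical value of about 2, so power exceeds 99.99%.
- Standardised effect giving 80% power: 0.572 at 49 per arm and 0.566 at 50. Multiplied by 1.849, this is 1.06 and 1.05 points.
- Equivalently, 110 matches the 3.15-point difference at 80% power only if the SD is about 3.15/0.572 = 5.5.

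**If the ± figures were standard errors.** This is an assumption that section 2.8 speaks against, and the pilot's size is not given. With m patients per pilot arm the SD would be 1.849 × √m.

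| Assumed m | SD | Required total |
|---|---|---|
| 9 | 5.55 | 112 |
| 10 | 5.85 | 126 |
| 20 | 8.27 | 246 |

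The larger assumed pilots would leave 110 short of 80% power.

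**The case against.** The strongest reply is that the discrepancy is on the safe side. If the pilot figures are right, 110 gives nearly full power, a null result becomes more informative, and randomisation, endpoint, test and alpha are untouched. On this view it is a reporting slip. That is right as far as it goes: on its own inputs the trial is not underpowered, and a misread null result is a risk only if the true SD is larger or the true effect smaller than printed.

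A second reply is that investigators often discount an optimistic pilot effect, and a condensed article may omit that step. This is possible, but the section does not leave the derivation open. It lists the inputs and calls 110 the required number, and that is false for those inputs.

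A third point is that the standard-error explanation is weak, because section 2.8 describes ± as SD. That sentence concerns the trial's own data rather than the pilot, but it is the only definition available, so the explanation deserves a question and no more.

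Finally, the document does not show which number is wrong. An effect of 0.57 SD obtained by solving backwards from 110 must not be presented afterwards as the original design assumption.

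**Conclusion.** The concern holds. With the ± figures read as SDs of change, 1:1 allocation and the stated test, alpha, power and dropout, the requirement is 14 evaluable patients, or 16 randomised, against 110 stated. The choice of t or normal approximation, of rounding and of dropout convention moves the answer by a few patients; the gap is 94. Conversely, 110 patients give power above 99.99% for the stated effect, not 80%.

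The contradiction is certain; its cause is not. Either the total rests on inputs that are not printed, or the printed spreads are not SDs of change, or the power statement is wrong. It needs correcting because no other part of the article justifies the size of the primary comparison.

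**What to change.** First confirm from the pilot records what the ± figures are, and give the number of pilot patients per arm. Then rewrite section 2.7 in whichever way is true:

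- If 110 was derived from a different difference or SD, state those values and where they came from.
- If the pilot figures are correct and 110 was chosen for other reasons, give the reasons. Then state that about 99 evaluable patients provide over 99% power for 3.15 points, and 80% power for about 1.05 points (0.57 SD) at SD 1.85.
- If the pilot figures or the total are misprinted, correct them and rerun the calculation.

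In the first two cases the cost is one paragraph and enrolment stays at 110. In the third, enrolment needs another look only if the corrected inputs call for a different number.

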### Statistical analysis

2.8

Statistical analysis will be performed using SPSS v22.0 software. The measurement data is expressed as mean ± standard deviation, and Student *t* test, Wilcoxon rank-sum test, or Manne–Whitney *U* test after normality and homogeneity test. The count data is expressed as percentage (%) and *χ*^2^ test will be applied. *P* < .05 is considered statistically significant.

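### Section 2.8 leaves the primary test to preliminary normality and homogeneity checks, although section 2.7 sizes the trial on a t test; two of its three options are one test, and none compares means under unequal variances

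*Protocol article*

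**What the plan says.** Section 2.6 defines the primary endpoint as a continuous change score: "The primary outcome is the change of fatigue scores measured by cancer fatigue scale before and after the treatment".

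Section 2.7 sizes the trial on pilot means and SDs of that change ("the change of cancer fatigue scale scores in the treatment group was 6.65 ± 2.12, while 3.5 ± 1.53 in the control group"), under the heading of a t test: "Considering a 2-sided *t* test", "with 5% type I error at 80% power". With 10% dropout it arrives at 110 patients in total, or 55 per arm at 1:1 allocation.

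Section 2.8 does not single out the primary outcome. For all measurement data it lists Student t, "Wilcoxon rank-sum test, or Manne–Whitney" U, to be applied as the "test after normality and homogeneity test" indicates. It gives no level for the preliminary tests and does not say which result leads to which test. It lists no unequal-variance t test.

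**The concern.** The rule has three faults.

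- **The primary test depends on the data.** Sample size and analysis should refer to the same test of the same quantity. Here the sample size refers to a difference in mean change, while the analysis may become a rank comparison, depending on a preliminary look at the trial data.
- **The list does not offer what it appears to offer.** With two independent groups, the Wilcoxon rank-sum and Mann–Whitney U tests are one test under two names. If a paired signed-rank test was meant, the wrong test is named.
- **The homogeneity check has no suitable alternative behind it.** When variances differ, the usual way to keep a comparison of means is an unequal-variance t test or robust standard errors. The only listed alternatives to Student t are rank tests, which answer a different question and do not cure unequal variances. The plan's own pilot SDs differ between the arms.

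At stake is whether the primary p-value and the planned effect measure refer to the same thing, and whether that is settled before the data are seen.

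**Working it through.** **Inputs.** Section 2.7: mean change 6.65 (SD 2.12) v 3.5 (SD 1.53), two-sided 5% level, 80% power, 10% dropout, total 110. That is 55 per arm, or 55 × 0.9 = 49.5 after dropout, so I use 49, 50 and 55. Assumed: 5% level for the preliminary tests (1% as an alternative), normal data unless stated, and pilot SDs equal to the true SDs.

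**1. The plan's figure.** Difference 6.65 − 3.5 = 3.15. Pooled SD = √[(4.494 + 2.341)/2] = 1.849. Per arm n = 2 × (1.960 + 0.842)² × 1.849² / 3.15² ≈ 5.4, so 6 (7 by the exact t calculation). The total is 12–14, or 14–16 with dropout. The stated inputs do not give 110. That is a separate matter, but the rates below depend on N = 110.

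**2. Variance ratio.** 2.12² / 1.53² = 4.494 / 2.341 = 1.92.

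**3. How often homogeneity would be rejected.** For the two-sided F test with n per arm, power ≈ P(F > c/1.92), where c is the 97.5% point of F on (n−1, n−1) degrees of freedom; the lower tail is negligible. At n = 50, c = 1.762 and c/1.92 = 0.918, which gives 0.617. Levene's test was simulated.

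| Test, level | n = 49 | n = 50 | n = 55 |
|---|---|---|---|
| F, 5% | 61% | 62% | 66% |
| Levene, mean-centred, 5% | 54% | 56% | 60% |
| Levene, median-centred, 5% | 52% | 53% | 57% |
| F, 1% | 36% | 37% | 41% |
| Levene, mean-centred, 1% | – | 30% | 34% |

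Adding a Shapiro–Wilk test in each arm at 5%, at least one preliminary test rejects in about 57–64% of trials with normal data. With heavy-tailed, skewed or uniform data and the same SDs, the figure at 50–55 per arm is 78–99%.

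**4. Sensitivity to the assumptions.** With equal true SDs, Levene rejects in about 5% of trials at 50 per arm. At 7 per arm, the size that the stated inputs give, the F test rejects in about 11%. The pilot's size is not stated. A sample variance ratio of 1.92 has two-sided F-test p = 0.35 at 10 per arm, 0.16 at 20 and 0.08 at 30, and reaches 0.05 only near 38 per arm.

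**5. Redundancy.** On one simulated two-group data set, the rank-sum and Mann–Whitney routines (normal approximation, no continuity correction) both returned p = 0.3926.

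**6. Consequences at 50 per arm.**
- Null, unequal SDs, preliminary tests applied mechanically (homogeneity and normality): type I error 5.3%, against 5.2% for t alone and 5.4% for Mann–Whitney alone. Switching on normality only gave 5.6% (normal data) and 5.0% (gamma data) in 5,000 trials, with a simulation standard error of √(0.05 × 0.95/5000) ≈ 0.3 percentage points.
- Null, reporting whichever of t and Mann–Whitney is significant: about 6.6%.
- True difference 3.15: every test rejects in 100% of trials, with no disagreements.
- True difference 1.036, about the effect that 50 per arm detects with 80% power: power 79% (t) and 77% (Mann–Whitney); the two disagree in about 6% of trials.

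**The case against.** A reader might infer that the planned t test would more often than not be abandoned. The document does not support that as a plain statement. It rests on a 5% preliminary level, on a failed homogeneity check leading to a rank test, and on pilot SDs from a study of unstated size being the true ones. None of these is in the text, and step 4 shows how far the rate moves when they change. If failed homogeneity was meant to lead to a Welch test, the t test would survive in another form.

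A reader might also infer a serious error-rate problem, or a choice made on unblinded data. Neither stands. Mechanical pre-testing leaves type I error near 5%, and at the stated effect the choice of test cannot alter the conclusion. Section 2.4 does not describe the analyst's access to allocation, and a homogeneity test can be run on coded groups. Nor would the scale-point summary disappear, since section 2.8 reports means and SDs whichever test is used.

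The duplicate name adds no analytic freedom, because one test gives one p-value. It is an error of wording.

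Finally, this is a condensed article, and detailed branch rules commonly sit in a statistical analysis plan. That answers a complaint about missing detail, but the objection here is to a rule the article does state. The rule covers the primary outcome and does not match the test used for sizing.

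**Conclusion.** The point holds as one of specification. Section 2.8 makes the between-group test of the primary outcome depend on preliminary tests of the trial data, while section 2.7 commits to a t test of a mean difference. Two of the three options coincide, and none is a comparison of means valid under unequal variances, although the pilot variance ratio is 1.92.

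The share of trials in which homogeneity would be rejected is conditional: about 52–66% under the assumptions above, about 30–41% at a 1% level, and about 5% if the true SDs are equal. The effect on type I error is negligible when the rule is applied mechanically (about 5.0–5.6%). The practical cost is that the primary test, and the quantity it addresses, are not settled beforehand. This could affect the result only if the true effect is much smaller than the 3.15 points assumed.

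**What to change.** In section 2.8, delete the preliminary-test rule for the primary outcome and name one analysis to be used whatever the distribution:

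- the between-group difference in mean change in cancer fatigue scale score, adjusted for the baseline score (already collected), with heteroscedasticity-robust standard errors; or, if no adjustment is wanted, a Welch t test;
- in either case, a 95% confidence interval in scale points;
- the Mann–Whitney U test, under one name, as a sensitivity analysis only.

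Baseline adjustment is not needed to cure the pre-testing fault; a Welch test alone would do that.

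The cost is a change of wording. The loss of power is negligible at about 50 per arm: in a simulation of 40,000 trials with SDs 2.12 and 1.53 and a true difference of 1.036, Welch and Student t both had power of 79%.
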